### Other concomitant treatment

Other medication other than that described above, which is considered necessary for the patient’s safety and well being, may be given at the discretion of the Investigator and recorded in the appropriate sections of the Case Report Form.

In addition, any unplanned diagnostic, therapeutic or surgical procedure performed during the study period must be recorded in the eCRF.

## Post Study Access to Olaparib

After the end of the study, patients still on study therapy at that time will continue to receive olaparib outside the study until they continue to derive clinical benefit from treatment in the view of the investigator and no other criteria for treatment discontinuation are met.

# Statistical ANALYSES BY ASTRAZENECA

## Statistical considerations

Analyses will be performed by AstraZeneca or its representatives.

A comprehensive statistical analysis plan (SAP) will be prepared and any subsequent amendments will be documented, with final amendments completed prior to the data cut for the primary analysis.

## Sample size estimate

The sample size of approximately 220 patients is driven by the need to enrol an adequate number of patients to help understand the efficacy and safety of olaparib with the tablet formulation. Around 46 patients with BRCAm ovarian cancer will be enrolled assuming that BRCA mutation rate is 21%.

The primary analysis will be performed after the accumulation of 132 progression or death events which corresponds to 60% maturity. Assuming a median PFS value of 8.4 months, 132 PFS events will provide a 95% confidence interval of (7.1 m, 10.0 m) for the median PFS. Assuming a median PFS of 19.1 months in the BRCA mutated patients, 27 PFS events (60% of 46 BRCA mutated patients) will provide a 95% confidence interval of (13.1 m, 27.9 m) for the median PFS.

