## Efficacy assessments

### CT and MRI scans tumour assessments (Modified RECIST 1.1)

Following the baseline assessment, subsequent tumour assessments according to modified RECIST 1.1 should be performed every 12 weeks (±1week) for the first 72 weeks and then every 24 weeks (± 1 week) thereafter, relative to the date of enrolment, up to objective disease progression by RECIST.

For those patients with no evidence of disease at baseline, following a clinical complete response to chemotherapy, progression is defined by the detection of new lesions on follow up radiological assessments (modified RECIST 1.1).

The imaging modalities used for RECIST assessment will be CT or MRI scans of the neck, chest, abdomen and pelvis with other regions as clinically indicated for the assessment of disease. Any other sites at which new disease is suspected should also be appropriately imaged. The methods of assessment of tumour burden used at baseline must be used at each subsequent follow-up assessment.

Radiological examinations performed in the conduct of this study should be retained at site as source data.

All treatment decisions will be based on site assessment of scans.

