### Analysis of the primary variable (s)

PFS will be analysed when approximately 132 progression events have occurred in the study (60% maturity). This analysis will address the primary objective of the trial. The updated results will also be provided at the final analysis.

A Kaplan-Meier (KM) plot of PFS will be presented. Summaries of the number and percentage of patients experiencing a PFS event, and the type of event (progression or death) will be provided along with median PFS and 95% confidence interval.

The analysis on PFS will be based on RECIST 1.1 criteria assessed by investigators, and using all scans regardless of whether they were scheduled or not. The estimated PFS rates at 6 months, 12 months and 24 months will be summarised (using the KM curve) for all patients.

The number of patients prematurely censored will be summarised together with baseline prognostic factors of the prematurely censored patients. A patient is defined as prematurely censored if they had not progressed and the latest scan prior to the date of cut off (DCO) was more than one scheduled tumour assessment interval (+ 2 weeks) prior to the DCO date.

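### The stated precision for median PFS (7.1 to 10.0 months at 132 events) is that of an exponential model, while the planned analysis is Kaplan-Meier, for which about 6.9 to 10.2 months is the matching figure

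*Protocol*

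**What the plan says.** Section 8.2 of the protocol, repeated in the synopsis under Statistical methods, gives the expected precision for the primary endpoint. "Assuming a median PFS value of 8.4 months", it says, "132 PFS events will provide a 95% confidence interval of (7.1 m, 10.0 m) for the median PFS". The cut is at "132 progression or death events which corresponds to 60% maturity". The same paragraph gives 13.1 to 27.9 months for BRCAm patients, from 27 events and an assumed median of 19.1 months. Neither place names a distribution or a formula; the synopsis only cites a survival-analysis textbook.

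On the analysis itself, section 8.5.1 says "A Kaplan-Meier (KM) plot of PFS will be presented", and that the number and percentage of patients with an event and "the type of event (progression or death) will be provided along with median PFS and 95% confidence interval". PFS rates at 6, 12 and 24 months are also to be read from the Kaplan-Meier curve. No exponential or other parametric model is planned in the protocol. The method for the confidence interval of the median is not named.

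On the timing of progression, section 5.1.1 says that tumour assessments "should be performed every 12 weeks (±1week) for the first 72 weeks and then every 24 weeks" thereafter.

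**The concern.** The precision statement and the planned analysis use different estimators. An exponential estimate of the median draws on all 132 events and all follow-up time through one hazard parameter. A Kaplan-Meier median depends on where the curve crosses 50%, and so on the density of events around that point. It is less efficient even when the exponential model is true. The protocol thus quotes the precision of an estimator that it does not plan to report.

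The study has one arm, and the protocol sets no test or power for it. This interval is therefore the only numerical statement of what 132 events buy in the whole population. A reader who compares the reported interval with the planned one should be comparing like with like.

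**Working it through.** **Inputs.** From section 8.2: median 8.4 months, 132 events, about 220 patients; for BRCAm, median 19.1 months, 27 events, 46 patients. Confidence level 95% (section 8.5.1), z = 1.96. Scan interval 12 weeks (section 5.1.1). The synopsis estimates enrolment from Q2 to Q4 2018, so accrual of roughly 3 to 9 months. Its uniform shape is my assumption.

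**Step 1: reproduce the printed intervals.** Exponential model, log scale: limits = median × exp(±1.96/√events).
- All patients: 1.96/√132 = 0.1706, so 8.4 × exp(±0.1706) = 7.08 to 9.96 months. This matches.
- BRCAm: 1.96/√27 = 0.3772, so 19.1 × exp(±0.3772) = 13.10 to 27.85 months. This matches.

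Two matches leave little doubt about the origin. The exact chi-square interval for an exponential median, 7.13 to 10.04 months, also rounds to 7.1 to 10.0. The untransformed exponential interval, 6.97 to 9.83, does not.

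**Step 2: the Kaplan-Meier median under the same exponential assumption.** With no censoring before the median, SE(log m) = (0.5/√n) / (m × f(m)). For an exponential distribution, m × f(m) = 0.5 × ln 2.
- SE = 1/(0.6931 × √220) = 0.0973, against 1/√132 = 0.0870 for the exponential estimate. The ratio is 1.118.
- 8.4 × exp(±1.96 × 0.0973) = 6.94 to 10.16 months. The width is 3.22 months, against 2.88.
- The shift is 7.08 − 6.94 = 0.14 month at the lower limit and 10.16 − 9.96 = 0.20 month at the upper.

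**Step 3: simulate the 132-event cut.** 220 exponential patients, uniform accrual, no drop-out, log-log limits, 2,500 runs per case.

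| Accrual (assumed) | Median KM limits, months | Log-width against stated |
|---|---|---|
| 3 months | 6.92 to 10.06 | +10% |
| 6 months | 6.92 to 10.12 | +12% |
| 9 months | 6.85 to 10.15 | +15% |

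Other choices of Kaplan-Meier limits do not remove the gap. At 8 months' accrual, plain limits gave 6.90 to 10.16 and log limits 7.03 to 10.37, each about 14% wider on the log scale. Assumed drop-out of 0.5 to 1.5% per month, over the same 3 to 9 months' accrual, gave about 13.5 to 17%.

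**Step 4: scan times.** 12 weeks is 84/30.4375 = 2.76 months, so scans fall at about 5.5, 8.3 and 11.0 months. Steps of the Kaplan-Meier curve will cluster there, and 7.1 and 10.0 both lie between scans.

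**Step 5: BRCAm on the same basis.** SE = 1/(0.6931 × √46) = 0.2127, so 19.1 × exp(±1.96 × 0.2127) = 12.6 to 29.0 months. This is optimistic at the upper end. With 27 events in 46 patients and 8 months' accrual, the simulated upper limit was not reached in about 46% of runs (drop-out 0.5% per month) to 82% (none).

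**The case against.** The strongest reply is that nothing is miscalculated. The printed interval is correct for a common planning approximation, and nothing depends on it. Section 8.2 says "The sample size of approximately 220 patients is driven by the need to enrol an adequate number of patients" to understand efficacy and safety, and sets no target width or success criterion. All of that stands, and it is why the point is minor.

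A second reply is that the protocol does not name the interval method for the median and that the SAP, which is not at hand, may do so. That is fair as far as the method goes. But Kaplan-Meier is the only estimation approach that section 8.5.1 describes, all three usual types of Kaplan-Meier limit gave a wider interval, and the figure in question is printed in the protocol.

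A third reply is that the size of the gap depends on exponential PFS. This is also right. For a Weibull distribution the Kaplan-Meier standard error is 0.0973 divided by the shape, so a shape of 0.0973/0.0870 = 1.12, a mildly rising hazard, gives the stated width.

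A reader might infer that the stated precision will not be delivered, or that the observed interval will usually be wider than promised. The documents support neither. They state no distribution, and under 12-weekly scanning with an underlying median of 8.4 months (8 months' accrual) the typical simulated limits were about 8.3 and 11.1 months, only about 2.8 months apart. There the interval moves rather than widens. How often the median or upper limit would jump to a later scan cannot be stated reliably. It depends on whether 8.4 months is the underlying or the scan-detected median, and section 1.3 gives it as the investigator-assessed median of the earlier phase II trial, which already includes that trial's detection delay.

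**Conclusion.** The point holds as a minor one. The interval of 7.1 to 10.0 months is an exponential-model figure whose assumption is not stated, printed for an analysis planned as Kaplan-Meier. On the exponential assumption and with continuous observation, the matching Kaplan-Meier figure is about 6.9 to 10.2 months. Its log-width is about 10 to 15% larger with 3 to 9 months' accrual, and it differs by about 0.1 to 0.2 month at each limit. A modestly rising hazard would close the gap, and the scan schedule means that neither smooth interval should be expected literally. The BRCAm interval has the same origin and is more fragile, because its Kaplan-Meier upper limit may not be reached.

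**What to change.** In section 8.2 and in the synopsis, restate the expected precision as about (6.9 m, 10.2 m) for the Kaplan-Meier median, and say that it assumes exponential PFS. Add a sentence that progression is detected at 12-weekly scans, so the observed limits will tend to fall at scan times (about 5.5, 8.3 and 11.0 months). Recompute the BRCAm interval on the same basis, or label it as an exponential-model figure and note that the Kaplan-Meier upper limit may not be reached.

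The cost is wording in two places and a slightly less favourable stated interval. The 220 patients, the 132 events and the planned analysis stay as they are. A supportive interval-censored estimate of the median would help readers see past the scan steps, but it is optional and could sit in the SAP.

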| Estimated date of PFS analysis* | Q2 2020 |  |

* Estimated date of 132^th^ PFS event

Study design

This is a prospective, open-label, single arm, multi-centre interventional study to assess the clinical efficacy and safety of olaparib maintenance monotherapy and will be conducted in patients with platinum sensitive relapsed (PSR) high grade epithelial ovarian, fallopian tube, or primary peritoneal cancer who are in response (complete response or partial response) to platinum-based chemotherapy.

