## Methods for statistical analyses

Data will be analyzed on the FAS population. The primary analysis will be performed at the time of accrual of 132 progression or death events in the 220 enrolled patients. The final analysis will be performed when approximately 60% OS maturity is achieved.

Data will be summarized using descriptive statistics as appropriate. Continuous variables will be summarised by the number of observations (n), mean, standard deviation (SD), median, quartiles (Q1 and Q3), minimum, and maximum. Categorical variables will be summarised by frequency counts and percentages for each category.

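### The 27 BRCAm PFS events behind the stated 13.1–27.9 month interval will not be there at the 132-event cut; about 15–18 are expected on the protocol's own medians

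*Protocol*

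**What the plan says.** Section 8.2, repeated in the synopsis under statistical methods, fixes one trigger: "The primary analysis will be performed after the accumulation of 132 progression or death events which corresponds to 60% maturity". For all patients it states: "Assuming a median PFS value of 8.4 months, 132 PFS events will provide a 95% confidence interval of (7.1 m, 10.0 m"). For the subset it states "Around 46 patients with BRCAm ovarian cancer will be enrolled assuming that BRCA mutation rate is 21"%, assumes a BRCAm median of 19.1 months, and concludes: "27 PFS events (60% of 46 BRCA mutated patients) will provide a 95% confidence interval of (13.1 m, 27.9 m) for the median PFS".

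Section 8.5 repeats the single trigger: "The primary analysis will be performed at the time of accrual of 132 progression or death events in the 220 enrolled patients". Section 4.4.4 also sets the cut at 60% PFS maturity. No BRCAm event trigger appears anywhere. PFS in the BRCAm population is the first secondary objective in section 2.2.

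Section 8.5.1 describes the analysis at about 132 events and says that updated results will follow at the final analysis, which is timed by about 60% OS maturity. Among the outputs: "The estimated PFS rates at 6 months, 12 months and 24 months will be summarised (using the KM curve) for all patients". The synopsis puts first patient in at Q2 2018 and last patient in at Q4 2018. Its "Estimated date of PFS analysis" is Q2 2020, footnoted as the date of the 132nd event.

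**The concern.** The 60% that yields 27 BRCAm events comes from the trigger for the whole trial. The two medians beside it, 8.4 and 19.1 months, mean that the subset accrues events far more slowly than the total. Both groups cannot stand at 60% on the same day.

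This sentence is the only precision statement for the first secondary objective. A reader planning on it expects a reached median with a two-sided interval at the primary readout. What is likely instead is a median that is not reached, or one resting on few patients and with no upper limit. The 24-month PFS rate has a related problem: under the same 8.4-month assumption nobody has been followed for 24 months at that cut.

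**Working it through.** **Inputs from the protocol.** 220 patients; 46 BRCAm (21%), hence 174 others; trigger 132 events; median PFS 8.4 months (all) and 19.1 months (BRCAm); enrolment Q2 to Q4 2018.

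**Assumptions not in the protocol.** Uniform accrual over R = 6 or 9 months, exponential PFS, no dropout (varied in step 6).

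**1. Reproduce the stated intervals.** Formula: median × exp(±1.96/√d).
- 8.4 months, d = 132: 1.96/√132 = 0.171, giving 7.08 to 9.96 (stated 7.1 to 10.0).
- 19.1 months, d = 27: 1.96/√27 = 0.377, giving 13.10 to 27.85 (stated 13.1 to 27.9).

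Both agree. The formula is not in dispute; the 27 is.

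**2. Hand check with equal follow-up.** At a median of 8.4 months, 60% events needs t = 8.4 × ln(0.4)/ln(0.5) = 11.1 months. At a median of 19.1 months, 1 − 0.5^(11.1/19.1) = 33%, which is 15.3 of 46.

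**3. Staggered entry.** Let F(T; m) be the average of 1 − 0.5^((T − u)/m) over entry times u from 0 to R. Solve 46·F(T; 19.1) + 174·F(T; m_N) = 132 for T, the time from first patient in. The 8.4 months can be read in two ways:
- A: it is the median of the mixture. Then (46/220)·0.5^(8.4/19.1) + (174/220)·0.5^(8.4/m_N) = 0.5, so m_N = 7.04.
- B: it applies to non-BRCAm patients only, so m_N = 8.4.

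| Reading | R (months) | T of 132nd event (months) | BRCAm events | BRCAm maturity |
| --- | --- | --- | --- | --- |
| A | 6 | 14.4 | 15.5 | 34% |
| A | 9 | 16.1 | 15.6 | 34% |
| B | 6 | 16.1 | 17.4 | 38% |
| B | 9 | 17.8 | 17.5 | 38% |

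Applying 8.4 months to all 220 patients gives 15.3–15.4 events.

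**4. When 27 arrive.** 46·F(T; 19.1) = 27 gives T = 27.4 months (R = 6) or 29.0 months (R = 9). Overall events are then about 185 (A) or 177–178 (B), that is 81–84% maturity, not 60%.

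**5. What Kaplan-Meier would return at the 132-event cut.** In 2,000 simulated trials per scenario, with exact event times and with 12-weekly scans:
- 95% range of BRCAm events: about 10–23; probability of 27 or more: at most 0.1%.
- Median reached: 14–26% of trials (A), 24–36% (B). Scan timing makes little difference.
- Finite upper 95% limit: 1–2%.
- When the median is reached it averages 12.7–16.2 months, below the true 19.1.

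The formula with 15 events gives 19.1 × exp(±0.506) = 11.5 to 31.7 months. That is nominal only, since the upper limit would seldom be obtained.

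**6. Sensitivity.**
- Annual dropout of 5–20% (reading A): 15.6–16.0 events.
- BRCAm share of 29% (22% germline plus about 7% somatic, section 1.1.2): about 22 of 64, still 34% maturity.
- BRCAm median of 11.2 months (phase II study, section 1.3): about 23 events, still below 27.
- Curve shape: with a cut before 19.1 months from first patient in, no BRCAm patient is followed past the assumed median, so expected events cannot exceed 50%, or 23 of 46, whatever the curve.

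**7. 24-month rate and calendar date.** T in step 3 is also the longest possible follow-up: 14–18 months. Nobody is at risk at 24 months. At 24 months after first patient in (roughly Q2 2020), 171–176 overall events (A) or 162–167 (B) are expected rather than 132, and about 23–24 BRCAm events, still below 27.

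**The case against.** The best defence is that the sentence is conditional: 27 events do give that interval, and the protocol does not say in words when they occur. This does not hold up. The 60% is that of the trigger sentence just before it, and no other BRCAm cut exists.

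The second defence is stronger. Section 8.5.1 already provides updated PFS at the final analysis, and section 9.3 expects the study to end by Q2 2024, well after 27–29 months from first patient in. A reader might infer that the BRCAm median or the 24-month rate is lost to the trial. The documents do not support that; both are delayed. But section 8.2 does not tie the 27 events to the update.

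Third, the study is single-arm and descriptive, and the protocol says: "The sample size of approximately 220 patients is driven by the need to enrol an adequate number of patients". No test or error rate depends on the BRCAm interval, so a reader should not conclude that the sample size fails.

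Fourth, the Q2 2020 date is an estimate and the trigger is the event count, so the mismatch with 8.4 months controls nothing. If PFS is longer than assumed, the cut moves later and more BRCAm events accrue. In simulation at 24 months (reading A, R = 6), 27 or more occur in 27% of trials and the upper limit is finite in 13%.

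Finally, version 4.0 is dated January 2023, after the estimated primary cut, so part of the correction may be retrospective. The protocol does not say whether that cut has taken place.

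**Conclusion.** The point holds: the overall 60% maturity was carried over to a subset that the plan itself assumes to progress much more slowly. At the 132-event cut about 15–18 of 46 BRCAm events (34–38%) are expected instead of 27, and the median will more often than not be unreached. The size rests on the protocol's two medians, 6–9 months of accrual and exponential PFS. The direction survives every variation in step 6.

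Two stronger readings should be avoided. The stated interval is not miscalculated; it belongs to a later date. Nor should 11.5–31.7 months replace it as the expected result, because at this cut a finite upper limit is itself unlikely. This should be fixed, but for a descriptive secondary objective with a planned update it is not critical.

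**What to change.** - **Section 8.2 and synopsis:** state that about 15–18 BRCAm events are expected at the 132-event cut and that the BRCAm median and its upper limit will probably not be estimable then. If a formula-based interval is shown (about 11.5–31.7 months for 15 events), label it nominal.
- **Sections 8.2, 8.5.1 and 8.5.2:** attach the 27-event, 13.1–27.9 month precision to the PFS update at the final analysis, or to a PFS update once 27 BRCAm events have occurred.
- **Section 8.5.1:** present the 24-month PFS rate at that update; at the 132-event cut give the 6- and 12-month rates.
- **Synopsis (minor):** reconcile the estimated Q2 2020 date with the 8.4-month assumption.

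Cost: wording, and at most one extra table run. No additional patients or visits. The stated BRCAm precision at the primary cut becomes less favourable.

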## Definitions of analysis sets

Full analysis set (FAS)

The full analysis set will include all subjects who received at least one dose of study treatment.

All analyses will be performed based on the FAS.

## Outcome measures for analyses

### Calculation or derivation of efficacy variable(s)

At each visit patients will be assigned a visit response of CR, PR, SD, PD, NE based on RECIST criteria or other methods depending on the status of their disease compared to baseline and previous assessments, based on the investigator assessment.

### Primary endpoint

PFS is defined as the time from first dose of olaparib until the date of investigator assessed disease progression according to RECIST 1.1 criteria or death (by any cause in the absence of disease progression) regardless of whether the patient withdraws from therapy or receives another anticancer therapy prior to disease progression. Patients who have not progressed or died at the time of analysis will be censored at the time of the latest date of assessment from their last evaluable efficacy assessment. However, if the patient progresses or dies after two or more missed visits, the patient will be censored at the time of the latest evaluable assessment. Given the scheduled visit assessment scheme, two missing visits will equate to more than 26 weeks since the previous RECIST assessment, allowing for early and late visits. If the patient has no evaluable visits or does not have a baseline assessment they will be censored at day 1 unless they die within two visits of baseline (25 weeks allowing for visit window).

The PFS time will always be derived based on scan/assessment dates not visit dates. Assessments/scans contributing towards a particular visit may be performed on different dates. The following rules will be applied:

Date of progression will be determined based on the earliest of the assessment/scan dates of the component that triggered the progression.

When censoring a patient for PFS the patient will be censored at the latest of the assessment/scan dates contributing to a particular overall visit assessment.

Overall visit assessments will be determined for each assessment (scheduled or unscheduled) and will contribute to the derivation of PFS.

Disease progression is defined as at least a 20% increase in the sum of the diameters of the target lesions (compared to previous minimum sum) and an absolute increase of > 5 mm, or an overall non-target lesion assessment of progression or a new lesion.

